### Statistical analysis

All efficacy analyses will be calculated for the intention-to-treat (ITT) and per-protocol (PP) populations. The ITT analysis will include all randomized patients who take at least one dose of the study medication. The patients whose infection status is unknown following treatment will be considered as treatment failures for the purposes of ITT analysis. The PP analysis will exclude patients with unknown *H. pylori* status following therapy and those with major protocol violations. The chi-square test, analysis of variance (ANOVA), or Fisher’s exact test, as appropriate, will be performed to compare demographic and baseline characteristics between treatment groups. The number and percentage of compliant patients will be tabulated according to the treatment regimen. Differences in compliance rates among treatment regimens will be assessed with 95% CIs. The chi-square test, ANOVA, or Fisher’s exact test, as appropriate, will be performed to compare adverse events and laboratory parameters between groups. The primary endpoint of the study is the *H. pylori* eradication rate after first-line treatment. The secondary endpoints are the frequency of adverse events, treatment compliance, and gastrointestinal symptomatic response after eradication.

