**Methods/design:**

In this multicenter, investigator-blinded, randomized trial we are recruiting adult patients with *H. pylori* infection from 15 hospitals in Korea to determine whether sequential or concomitant treatment is superior to standard triple therapy. Patients are randomly assigned to receive either standard triple therapy (lansoprazole, amoxicillin, and clarithromycin) for 7 days, or sequential treatment (lansoprazole and amoxicillin for the first 5 days, followed by lansoprazole, clarithromycin, and metronidazole for another 5 days) for 10 days, or concomitant therapy (lansoprazole, amoxicillin, clarithromycin, and metronidazole) for 10 days. The primary outcome is the rate of *H. pylori* eradication in the intention-to-treat population.

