### Randomization and masking

Randomization will be conducted using a centralized, web-based randomization system managed by the Medical Research Collaborating Center (https://mrcc.snuh.org) of Seoul National University Hospital, which uses permuted block randomization with a concealed and varying block size. Only the researcher at the Medical Research Collaborating Center is able to know which number indicates which treatment arm. To ensure concealed allocation, an independent staff member will dispense consecutively numbered, identically designed treatment packs that contain sealed bottles of study drugs. Physicians who are unaware of treatment assignment will manage all study participants. Participants will not be blinded to group allocation.

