### Procedures

The standard protocol for this study is shown in Fig. 3. Before enrollment, *H. pylori* infection status will be determined by a rapid urease test, urea breath test, histology, and/or bacterial culture. The patients will complete a standard questionnaire to collect complete demographic data, including age, sex, medical history, family history, history of smoking and alcohol consumption, and gastrointestinal symptoms. The patients will receive a printed handout that provides directions for taking the medications correctly and how best to adhere to treatment. The follow-up period of this study after randomization will be 8 weeks and will include two visits with each subject (first visit at 3 or 4 weeks after allocation, second visit 5–8 weeks after allocation). Adverse events and compliance will be evaluated at the first visit after allocation. At the second visit, the efficacy of *H. pylori* eradication therapy will be determined. In all subjects, a urea breath test will be conducted to assess *H. pylori* status at the fourth to sixth week after the end of *H. pylori* eradication therapy. A staff member blind to the eradication arm of each patient will perform the urea breath tests. The cutoff values will be set at 2% for the capsule urea breath test and 4.8% for the conventional urea breath test. Eradication will be defined as a negative result for the urea breath test. A Standard Protocol Items: Recommendations for Interventional Trials (SPIRIT) checklist is provided as an additional file (Additional file 1).

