### Tolerability and adherence

Drug tolerance and patient compliance will be evaluated at the end of treatment. Drug tolerance will be investigated by questioning patients about possible side effects, such as nausea, vomiting, dry mouth, diarrhea, constipation, rash, dizziness, disorientation, and candidiasis. Before treatment, the patients will be informed of the common adverse events associated with the study drugs and will be asked to record these symptoms during treatment in provided diaries. The adverse events will be assessed according to a 4-point scale: none, mild (discomfort annoying but not interfering with daily life), moderate (discomfort sufficient to interfere with daily life), and severe (discomfort resulting in discontinuation of eradication therapy) [24]. Incapacitating or life-threatening complications will be classified as serious and will be reported to a clinical research associate. Adherence to treatment will be assessed by providing all patients with a prestructured printed table with all dosages illustrated and then asking them to tick each time a pill was consumed and bring back the table along with any tablet not consumed, which will be counted. In cases of discrepancies between the structured printed table and residual medication, the latter will be taken into account to evaluate the patient’s adherence. Good compliance will be defined as the use of at least 80% of the total medication prescribed.

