### Sample size

Several studies have demonstrated that the eradication rate of standard triple therapy is approximately 75% in Korea [25]. The eradication rate of sequential or concomitant therapy has been reported to be more than 80% [23, 26]. To obtain the optimal eradiation rate, an efficacy greater than 85% is needed for each treatment [27]. Therefore, we hypothesized that the eradication rate would be superior in the sequential or concomitant therapy groups, with a 10% difference compared with the rate for standard triple therapy (85% vs. 75%). To demonstrate this 10% difference in the eradication rate using a statistical power of 80% and with the assumption of a one-sided error rate of 0.025, the protocol requires at least 909 randomly assigned participants. The sample size in this trial was estimated according to the following formula:$$ n=\frac{{\left\{{\mathrm{z}}_{\alpha}\surd 2P\left(1-P\right)+{\mathrm{z}}_{\beta}\surd {P}_1\left(1-{P}_1\right)+{P}_2\left(1-{P}_2\right)\right\}}^2}{{\left({P}_1-{P}_2\right)}^2} $$

To allow for possible dropouts, defined as patients who fail to present or to follow the medication instructions, 1137 subjects will be required.

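### The primary set called ITT is a modified ITT: randomised patients who never start treatment are left out, and participants who know their arm may fail to start at different rates

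*Protocol article*

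**What the plan says.** The abstract (Methods/design) places the primary outcome, the rate of "eradication in the intention-to-treat population". The Statistical analysis section then defines the set: "The ITT analysis will include all randomized patients who take at least one dose of the study medication". The next sentence there deals with missing outcomes: "The patients whose infection status is unknown following treatment will be considered as treatment failures for the purposes of ITT analysis".

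Three other sections bear on the point:

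- Randomization and masking: "Participants will not be blinded to group allocation". Treating physicians are unaware of the assignment.
- Trial design and study setting: the control is three drugs for 7 days. The sequential arm is two drugs for 5 days and then three drugs for 5 days. The concomitant arm is four drugs for 10 days.
- Tolerability and adherence: patients tick a dosing table and "bring back the table along with any tablet not consumed, which will be counted". Procedures adds the timing: "Adverse events and compliance will be evaluated at the first visit after allocation", which is 3 or 4 weeks after allocation.

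**The concern.** An intention-to-treat comparison keeps every randomised patient in the assigned arm, so that the groups differ only by chance and by treatment policy. A one-dose condition is applied after randomisation. It does little harm where the decision to start cannot depend on the arm, as under full blinding. Here the participant knows the arm and the regimens are visibly different in burden, so the decision to start can depend on it.

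A randomised patient known not to have started is outside the set. The failure rule cannot bring that patient back, because it applies only to patients already in the ITT analysis. If non-starting differs between arms, the denominators are cut by different fractions. The primary difference then moves away from the all-randomised difference that the ITT label promises, and it can move either way.

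**Working it through.** **Inputs from the protocol.** Sample size gives assumed eradication rates of 75% (control) and 85% (experimental), a difference of 10 points, a one-sided error rate of 0.025, and 909 participants, or 1137 with dropouts. Allocation is 1:1:1.

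**The plan's own figure.** 909/3 = 303 per arm. 303/(1 − 0.20) = 378.75, rounded up to 379, and 3 × 379 = 1137. The allowance is therefore 20%, which is implied and not stated. It covers "possible dropouts, defined as patients who fail to present or to follow the medication instructions", a mixture of non-attendance and poor adherence. It is not a non-starter rate, and the document gives none.

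**Assumptions.** Let d be the share of an arm left out because no dose was taken. The values of d below are hypothetical. Patients left out are taken to be failures when all randomised patients are counted.

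**Formula.** Rate in the one-dose set = rate in all randomised / (1 − d).

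**Results with all-randomised rates of 75% and 85% (10.0 points).**

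| Left out, control / experimental | Control | Experimental | Difference |
|---|---|---|---|
| 2% / 5% | 0.75/0.98 = 76.5% | 0.85/0.95 = 89.5% | 12.9 points |
| 5% / 2% | 0.75/0.95 = 78.9% | 0.85/0.98 = 86.7% | 7.8 points |
| 2% / 2% | 0.75/0.98 = 76.5% | 0.85/0.98 = 86.7% | 10.2 points |

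**Results with equal all-randomised rates of 75%.** Leaving out 2% of control and 5% of experimental gives 78.9% − 76.5% = 2.4 points where the all-randomised difference is zero. With 379 randomised per arm, the analysed numbers are 379 × 0.98 = 371.4 and 379 × 0.95 = 360.1. The standard error is √(0.765 × 0.235/371.4 + 0.789 × 0.211/360.1) ≈ 0.031. The chance of declaring superiority at one-sided 0.025 is then about P(Z > 1.96 − 0.79) = 12.0%, against a nominal 2.5%. With 0% and 2% left out, the shift is 1.5 points and the chance is 7.1%. Equal shares leave no false difference.

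**Level of each arm.** Equal shares hardly move the difference but do raise both rates. Sample size asks for more than 85% from each treatment. An all-randomised rate of 83.3% reads as 0.833/0.98 = 85.0% once 2% are left out.

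**The case against.** The strongest reply is that the departure from randomisation is only as large as the number of true non-starters, which may be very small. These patients consented after being told the risks and benefits. Treating physicians and breath-test staff do not know the arm, so exclusion driven by investigators is unlikely. The rule is stated openly in advance, and with few, balanced exclusions the effect on the difference is about 0.2 points. All of this stands as a limit on size. None of it prevents a participant from declining a regimen that he or she knows, and the balance between arms cannot be assumed beforehand.

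A reader might go further and infer that dosing can be known only from returned tables and tablets, so that patients who never come back also drop out and the failure rule is defeated. The protocol does not support this:

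- Nothing in it says that a missing table means no dose was taken.
- The natural reading of the failure rule keeps a patient who received the drugs and never returned, as a failure.
- Tolerability and adherence uses the table and tablet count to measure compliance against an 80% threshold, not to decide entry to the ITT set.
- That section also provides symptom diaries and questioning about side effects, although these too need contact with the patient.

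How undocumented dosing is classified may be settled in the full protocol or the SAP, neither of which is shown.

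The figures are also open to challenge. Shares of 5% in one arm are easier to believe if non-returners are dropped, which is not established. If burden is the reason for not starting, the longer regimens would be expected to lose more patients, but the document gives no data either way. Both directions are therefore shown.

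**Conclusion.** The point holds for known non-starters and for the label. The primary set is a modified ITT called ITT. It removes randomised patients after allocation, for reasons that can depend on an arm the participant knows, and the failure rule does not reach them. Loss of non-returners is possible but not established.

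The size is unknown. Under the hypothetical shares above, a 10-point difference becomes 12.9 or 7.8 points when 2% and 5% are left out in one direction or the other, and 10.2 points when 2% are left out of both arms. These figures rest on the planning rates of 75% and 85% and on counting those left out as failures. They measure distance from the all-randomised comparison. They do not show that the trial will be biased by that amount, or that randomisation is lost as a whole. The change is worth making because it removes a possible bias from the primary comparison at little cost.

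**What to change.** In Statistical analysis, define the primary ITT set as all randomised patients, analysed in the assigned arm, with unknown infection status counted as failure whether or not a dose was taken. Keep the at-least-one-dose set as a sensitivity analysis and label it modified ITT. Report the number of non-starters by arm.

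This is one sentence in the protocol, repeated in the SAP. It needs no new data and leaves 909 and 1137 as they are. Trial status reports enrolment at 75% of target, so the change can still precede the analysis.

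The main cost is slightly lower reported rates: 85% among starters becomes 0.85 × 0.98 = 83.3% if 2% do not start. Power falls somewhat too. If 75% and 85% are the rates among starters and 2% of each arm do not start, power with 379 per arm at one-sided 0.025 goes from 92.8% in the one-dose set to 90.8%. If 2% of control and 5% of experimental do not start, it goes from 92.4% to 66.2%, because the all-randomised difference is then 0.8075 − 0.735 = 7.25 points. That drop reflects a smaller effect of assignment, which an ITT analysis is meant to show.

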### Ethics and dissemination

The study is being conducted in accordance with Declaration of Helsinki standards and Food and Drug Administration regulations regarding good clinical practice. All participants will have been informed of the possible risks and benefits of participating in this clinical trial. After being provided sufficient time to ask questions, participants will be provided an informed consent form that was approved by the local institutional review board. A signed copy of the consent form will be maintained with the study records. Trial participants will be provided a unique participant identification number to maintain confidentiality, and no protected health information will be disseminated. Trial results will be disseminated through scientific conference presentations and by publication in scientific journals.

## Discussion

The Korean College of Helicobacter and Upper Gastrointestinal Research proposed revised guidelines in 2013 [10, 28]. These revised guidelines recommend standard triple therapy including a conventional PPI, clarithromycin, and amoxicillin as the primary eradication regimen with a high level of evidence and strong recommendation grade. Furthermore, only this regimen is reimbursed by the Korean government and health insurance system.

However, a recent study using a nationwide Korean database demonstrated that the eradication rate of clarithromycin-based standard triple therapy is 73% [9]. Furthermore, a comprehensive meta-analysis of Korean reports indicated an overall eradication rate of 74.6% by ITT analysis and 82.0% by PP analysis [29]. More importantly, the eradication rate has decreased significantly over the past 10 years [30]. However, this decreasing trend was reported to be different in subgroup analysis, depending on the geographic area. This appeared to be caused by the amount of macrolide antibiotic used [30]. In this respect, clinical guidelines for *H. pylori* eradication should be modified on the basis of results of a nationwide trial, given the variation in eradication rates after standard triple therapy in each region. Most randomized studies involving the efficacy of first-line treatment were conducted at a single center, and very few multicenter studies have been published to date [29]. A recent nationwide randomized trial revealed that sequential therapy provides higher eradication rates than does standard triple therapy as a first-line therapy in Korea, with ITT eradication rates of 70.8% for standard triple therapy and 82.4% for sequential therapy [26]. However, as the authors mentioned, there was a lack of uniformity in the methodologies used among different institutions.

The efficacy of sequential or concomitant therapy for first-line treatment has been reported to be superior to that of clarithromycin-based standard triple therapy by many Korean researchers, which is in agreement with data from other countries. Nevertheless, a pooled analysis showed that sequential treatment led to suboptimal eradication rates in a Korean population, perhaps due to high rates of resistance to clarithromycin and metronidazole [19]. Hence, regional variations in antibiotic resistance need to be understood so that the global optimal protocol for different Korean regions can be determined.

This study is designed to assess the two regimens of greatest interest at present. Furthermore, we will enroll patients from across the different regions of Korea, and a sufficient sample size will be obtained to answer the study question in a statistically rigorous manner. This study will produce vital evidence that will lead to revisions to guidelines concerning first-line treatment regimens for *H. pylori* infection, better eradication rates, and an improved patient quality of life.

### Trial status

Recruitment is ongoing. The first patient was randomly assigned to a treatment group in November 2016. Patient enrollment reached 75% of target number.

## Abbreviations

ANOVA: Analysis of variance
iCReaT: Internet-based Clinical Research and Trial management system
ITT: Intention to treat
PP: Per protocol
PPI: Proton pump inhibitor
SPIRIT: Standard Protocol Items: Recommendations for Interventional Trials
